#### Inclusion criteria

Patients diagnosed with CID are eligible to participate in the study. Inclusion criteria are (1) aged between 18 and 65 years, right-handed, any gender; (2) meets the CID diagnostic criteria in the International Classification of Sleep Disorders-Third Edition (ICSD-3) [43], and meets the criteria for spleen and stomach disharmony syndrome in the Clinical Terminology of Traditional Chinese Medical Diagnosis and Treatment—Syndromes (GB/T 16751.2-1997) [44]; (3) Pittsburgh Sleep Quality Index score above 7 (PSQI score > 7); (4) not taking any medication or health care products to improve sleep quality and experienced GI diseases at least 2 weeks before study enrollment; (5) has not participated in other clinical trials within the last month; and (6) agrees to voluntarily participate in the study and signs an informed consent form.

The HCs must meet the following inclusion criteria: (1) passes the neuropsychological tests and reports good sleep quality; (2) no GI symptoms; (3) all physiological indexes within the normal range following a physical examination, and no previous functional or organic disease or head injury; and (4) agrees to voluntarily participate in the study and signs an informed consent form.

#### Exclusion criteria

Patients with any one of the following criteria will be excluded: (1) any severe conditions of the cardiovascular, cerebrovascular, liver, kidney, and hematopoietic systems; (2) secondary insomnia caused by drugs, cervical spondylosis, or other diseases; (3) history of psychiatric and neurological disorders or head trauma with loss of consciousness; (4) abuse of psychotropic drugs for anxiety and depression or sedative and hypnotic drugs; (5) pregnant, preparing for pregnancy, or lactating; and (6) any MRI contraindications such as claustrophobia, cardiac pacemaker, defibrillator, heart stenting, metal dentures, or intrauterine device.

The exclusion criteria for the HC are the same as for the patients.

#### Withdrawal criteria

Participants with any of the following conditions will be withdrawn: (1) complications that affect safety, (2) serious adverse events, and (3) unwilling to follow the study protocol for examination and treatment.

### Sample size

According to the previous studies [45, 46], the mean difference of PSQI scores between acupuncture and sham acupuncture was at least 2.7. We expect the mean PSQI score to decrease by 4.5 points in the acupuncture group and 1.8 points in the control group after treatment. When α was 0.05, 1-β was 0.9, and standard deviation was 3, the calculated sample size was 27. Given that this is a neuroimaging study, sample size requirements in the neuroimaging field should also be taken into account. At present, there is no accepted standard for the sample size calculation of imaging studies. The requirements of imaging studies [47, 48] and previous similar studies [49, 50] suggest that 12–26 individuals in each group is reasonable sample size for data analysis. To allow for potential problems such as subject dropout and invalid imaging data owing to head movements, a sample of 30 patients in each group is considered reasonable.

### Randomization and allocation concealment

A researcher ([name]), who will not be involved in the process of patient recruitment and treatment, will use SAS 9.2 software (SAS Institute Inc., Cary, NC, USA) to generate 60 random numbers and 60 serial numbers. Then, he will divide them into two groups based on random numbers and get the group numbers. These random numbers, serial numbers, and group numbers will be placed in opaque, sealed envelopes. Each sealed envelope will be numbered in sequence and kept in a safe place until the study is complete. If participants met the inclusion and exclusion criteria, envelopes with the same serial number will be opened in the order of enrollment by the same researcher ([name]) and the treatment allocation results will be forwarded to the acupuncturists. Except for the acupuncturists and the researchers who opened the envelopes, neither the participants nor the other researchers would know the participants' groups.

### Blinding

The blinding of acupuncturists is quite difficult to achieve [51]. Patients will be told that they would be randomly assigned to one of two effective interventions after enrollment. During the treatment, patients will receive treatment in acupuncture treatment rooms with compartments to avoid relevant communication between patients. Acupuncturists will also be required to keep treatment plans secret. The names of the treatment and control groups will be replaced with meaningless letter combinations to prevent outcome assessors and statisticians from knowing how patients are grouped. Therefore, only patients, outcome assessors, and statisticians will be fully blind in this study.

### Interventions

Treatments will be performed by certified acupuncturists with at least 3 years of acupuncture experience. Disposable sterile filiform needles (XingLin acupuncture needle, Φ0.25 × 25 mm/Φ0.25 × 40 mm, Tianjin Yi Peng Medical Instrument Co., Ltd., China) will be used. Both the acupuncture and sham acupuncture treatments will comprise 20 sessions over 4 weeks (five sessions per week).

#### Real acupuncture group

Patients in the real acupuncture group will receive acupuncture treatment on the acupoints *Baihui* (DU20), *Zhongwan* (RN12), and *Zusanli* (ST36) with disposable sterile filiform needles. All acupoints will be located according to the World Health Organization Standard Acupuncture Locations and are shown in Table 1 and Fig. 3. Needles in DU20 will be inserted 0.5–1 cun (a unit of measurement in acupuncture, 1 cun = 25 mm) using horizontal needling. Needles in RN12 and ST36 will be inserted 0.5–1.5 cun using perpendicular needling after skin disinfection. After the needle enters into the skin, needles will be manipulated by twirling, lifting, and thrusting to generate the sensation of de qi in the local tissue. The experience of de qi is characterized by sensations of numbness, heaviness, or distension felt by the patient. All needles will be retained for 30 min.

**Table 1 Tab1:** Acupoint locations for the real acupuncture group

Acupoints	Locations
*Baihui* (DU20)	The intersection of the crown midline and the apex of the ears
*Zhongwan* (RN12)	On the upper abdomen, anterior median line, four cun^a^ above the navel
*Zusanli* (ST36)	On the outside of the calf, three cun below *Dubi* (ST35)^b^

^a^According to the theory of traditional Chinese medicine, the navel is 8 cun below the xiphoid process

^b^ST35 is located on the lateral depression of the patellar ligament

**Fig. 3 Fig3:**
[figure not shown]
Location of acupoints and sham acupoints. SA, sham acupoint

#### Sham acupuncture group

The sham acupuncture group will receive a superficial skin penetration treatment at sham acupoints (SA). These SA are located near real acupoints (2 cm lateral from DU20, RN12, and ST36) but do not belong to any known meridian and are not conventional acupoints. The SA locations are shown in Table 2 and Fig. 3.

**Table 2 Tab2:** Sham acupoints locations for the sham acupuncture group

Sham acupoints (SA)	Locations
`SA 1	2 cm to the right of DU20
SA 2	2 cm to the right of RN12
SA 3	2 cm outside of ST36

cm, centimeter

Superficial skin penetration at SA, without needle manipulation for de qi, is a common sham acupuncture method used in many acupuncture randomized controlled trials [52]. Patients in this group will undergo an acupuncture procedure similar to the one received by patients in the real acupuncture group.

### Concomitant medication

Patients will be advised to avoid medication as much as possible during the study. Following medical ethical principles, if patients’ insomnia symptoms do not significantly improve and they cannot tolerate their insomnia, they may temporarily take sleeping drugs. Except for sleeping drugs, other drugs will be not allowed to be used in the trial. Researchers will record the name, dosage, and time of the drugs taken in detail in the Case Report Form (CRF).

### Multimodal MRI data acquisition

MRI examinations will be performed at the MRI Center at the University of Electronic Science and Technology of China using a 3.0 T MRI scanner (GE Discovery MR750, USA) equipped with a standard 8-channel head coil. MRI scans will be assessed at baseline and after 4 weeks. Subjects will be told to eat light food; avoid drinking strong tea, coffee, and wine; and avoid strenuous exercise the day before the scan. To prevent head movements affecting the image, foam pads and towels will be used to hold the head. During the MRI examination, all subjects will wear earplugs and be instructed to relax with their eyes closed and keep their heads clear. The scanning procedure produces a three-dimensional T1 image (3D-T1), a blood oxygenation level-dependent fMRI (BOLD-fMRI), a DTI sequence, and a proton ^1^H-MRS. The 3D-T1 scanning parameters will be as follows: repetition time (TR)/echo time (TE) = 5.988/1.972 ms, slice thickness = 1 mm, slice number = 154, field of view (FOV) = 256 × 256 mm. The BOLD-fMRI scanning parameters will be as follows: TR/TE = 2000/30 ms, flip angle = 90°, slice number = 35, matrix size = 3.75 × 3.75, FOV = 64 × 64 mm, slice thickness = 4 mm. The DTI data will be obtained using the following parameters: FOV = 240 × 240 mm, TR/TE = 6800/93 ms, matrix size = 128 × 128, and slice thickness = 3 mm with no gap. The proton ^1^H-MRS asymmetric PRESS sequence includes TE1 = 25 ms, TE2 = 85 ms, TR = 2 s, and a 2 × 2 × 2 cm area of interest on the anterior cingulate gyrus will be selected [29].

### Outcome measures

The outcome assessments will be performed at baseline and after 20 treatment sessions. All outcome assessors will be trained in conducting interviews and performing measurements before the study begins and will follow a standard protocol. An overview of the outcome measurement at different time points is shown in Fig. 2.

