### Study design

This randomized, single-blind, sham-controlled neuroimaging study will be conducted at the affiliated hospital of Chengdu University of Traditional Chinese Medicine (CDUTCM), China. A total of 60 CID patients with GI disorder will be recruited using advertisements on posters and hospital networks. All patients meeting the inclusion criteria will randomly receive either 20 sessions of real acupuncture treatment or 20 sessions of sham acupuncture treatment. A multimodal MRI examination and evaluation will be performed at both baseline and the end of treatment. Additionally, 30 healthy controls (HCs) matched for age, sex, and education level will receive one multimodal MRI scan and a clinical assessment. A flowchart of the trial design is shown in Fig. 1, and the participant timeline is shown in Fig. 2.

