**Fig. 2 Fig2:**
[figure not shown]
Time schedule of enrolment, interventions and assessments. Eligible patients will be screened according to inclusion and exclusion criteria. These patients will then sign an informed consent form and undergo a medical examination. Eligible insomniacs will be randomly assigned to either the true or sham acupuncture groups and complete clinical and MRI assessments before treatment. After a 4-week treatment period, these patients will undergo clinical and MRI assessments again. In addition, adverse events will be recorded in the CRFs at any time during treatment. MRI, magnetic resonance imaging; PSQI, Pittsburgh sleep quality index; GSRS, gastrointestinal symptom rating scale; SAS, self-rating anxiety scale; SDS, self-rating depression scale

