### Data analysis

#### Clinical data analysis

Statistical analyses of the clinical data will be performed using SPSS 20.0 statistical software (IBM Corporation, Armonk, NY, USA) and supervised by a skilled statistician blinded to group allocation. The Kolmogorov–Smirnov test will be used to test the normal distribution of continuous variables. Continuous normally distributed data will be reported as means and standard deviations; continuous non-normally distributed data will be expressed as medians with interquartile ranges. Categorical data will be presented as frequencies or percentages.

For the demographic and clinical information at baseline, the chi-squared test or Fisher’s exact test will be used for comparison of dichotomous data. The two-sample t test will be used for normally distributed continuous data or the Mann-Whitney U test for non-normally distributed data. To compare baseline and post-treatment changes in the same group, we will use the paired t test. Covariance analysis using baseline data as covariates will be used to compare the effects of different interventions on continuous data. In addition, gender differences and age differences may influence the data results. Therefore, in order to avoid the influence of gender, age and other factors on the data, we will also adopt covariance analysis, taking gender, age, and other factors as covariates respectively, and conduct covariance analysis with continuous data. A p value < 0.05 will be considered statistically significant.

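### The post-treatment assessment is timed both by sessions received and by calendar, and withdrawal is not separated from outcome collection, so early stoppers may have no post-treatment PSQI

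*Protocol article*

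**What the plan says.** The protocol article describes the second assessment in four places:

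- Outcome measures: "The outcome assessments will be performed at baseline and after 20 treatment sessions".
- Fig. 2 legend: "After a 4-week treatment period, these patients will undergo clinical and MRI assessments again".
- Multimodal MRI data acquisition: "MRI scans will be assessed at baseline and after 4 weeks".
- Study design: "A multimodal MRI examination and evaluation will be performed at both baseline and the end of treatment".

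The Interventions section plans 20 sessions in each arm, five a week for 4 weeks.

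On leaving the trial, the Withdrawal criteria state: "Participants with any of the following conditions will be withdrawn: (1) complications that affect safety, (2) serious adverse events". The third ground is being "unwilling to follow the study protocol for examination and treatment". The section does not say whether a withdrawn participant leaves study treatment only, or outcome assessment and analysis as well.

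On analysis, the Clinical data analysis section states: "Covariance analysis using baseline data as covariates will be used to compare the effects of different interventions on continuous data". It names no analysis population. The only exclusion from analysis stated anywhere is of MRI data from patients who took drugs (Imaging data analysis), and that does not touch the PSQI.

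**The concern.** A time point defined by sessions received is reached only by patients who receive them all. Someone who stops after eight sessions never reaches it. Someone who misses sessions and makes them up after week 4 reaches it late. A calendar time point is reached by everyone. The document gives both and does not say which governs when they differ.

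The withdrawal wording adds to this. If withdrawal also ends outcome collection, a patient who stops on safety grounds or through unwillingness leaves with a baseline value only. There is a single post-baseline assessment, so no intermediate PSQI is available to fall back on.

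The first study aim is to confirm efficacy against sham, and the PSQI is a primary outcome. Randomisation protects that comparison only if outcomes are sought from everyone randomised. If stopping is related to outcome, a comparison of those who finished is no longer the randomised one. An analysis plan can name the population later, but it cannot recover a questionnaire that was never taken.

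**Working it through.** **1. Do the timing rules agree?** At five sessions a week, 20 sessions take 20 / 5 = 4 weeks, so a patient who attends as scheduled reaches both time points together. For other patients:

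| Patient | After 20 sessions | After 4 weeks |
|---|---|---|
| Attends as scheduled | week 4 | week 4 |
| Misses sessions and makes them up after week 4 | later than week 4 | week 4, with fewer than 20 sessions received |
| Stops early | never reached | week 4, if still followed |

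The last row depends on what withdrawal means, and the document does not define it.

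**2. The plan's own figures.** Inputs from the Sample size section: mean PSQI decrease 4.5 (acupuncture) and 1.8 (control), difference 4.5 - 1.8 = 2.7, SD 3, alpha 0.05, power 0.90, stated result 27. A two-sided two-sample t test gives power 0.889 at 26 per arm and 0.901 at 27, so 27 per arm is reproduced. The two-sided normal approximation gives 26. Enrolling 30 per arm corresponds to 10% loss, since 27 / 0.90 = 30. The article states no dropout rate, and this margin also covers unusable imaging data.

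**3. What a completer comparison would do.** Assumptions, none of which the document gives:

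- completers show the planned decreases of 4.5 and 1.8;
- early stoppers show no change;
- a share a of the real arm and a share s of the sham arm stops early.

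Then:

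- completer difference = 4.5 - 1.8 = 2.7
- as-randomised difference = (1 - a) × 4.5 - (1 - s) × 1.8
- error of the completer comparison = 4.5a - 1.8s

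| Loss, real / sham | As-randomised difference | Error of completer comparison |
|---|---|---|
| 10% / 10% | 4.05 - 1.62 = 2.43 | +0.27 (10% of 2.7) |
| 10% / 0% | 4.05 - 1.80 = 2.25 | +0.45 (17%) |
| 0% / 10% | 4.50 - 1.62 = 2.88 | -0.18 (-7%) |
| 20% / 20% | 3.60 - 1.44 = 2.16 | +0.54 (20%) |
| 20% / 0% | 3.60 - 1.80 = 1.80 | +0.90 (33%) |

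Under these assumptions the sign turns negative once 1.8s exceeds 4.5a, that is, once sham loss is more than 2.5 times real-arm loss. If stopping is unrelated to outcome, stoppers have the same mean change as completers in their arm and the error is zero. The 20% rows are twice the loss implied by the enrolment margin.

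**The case against.** The strongest reply is that all four timing statements describe one planned visit. Twenty sessions is the 4-week course, and Outcome measures itself refers to Fig. 2, whose legend uses the 4-week period for both clinical and MRI assessments. On that reading the session count is shorthand for the end of the course. This is a reasonable account of what was probably meant, and it stands for patients who attend as scheduled. It does not settle what happens to the others, and they are the only patients for whom the wording matters.

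Second, a reader might infer that the plan analyses completers only. The document does not say so. The covariance analysis carries no such restriction, the population may be set in an analysis plan that is not shown, and allowing for dropout in the sample size is routine and implies nothing about the population. This objection stands in full.

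Third, a reader might infer that any adverse event or missed session leads to withdrawal. The criteria are narrower: complications affecting safety, serious adverse events, and unwillingness that covers examination as well as treatment. A patient who refuses examination gives no outcome under any wording. This also stands, and it leaves the two safety grounds as the clearest cases in which a patient could still be assessed.

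Fourth, a reader might infer that the bias favours real acupuncture. The table shows that it need not. Sham needling also penetrates the skin in a similar procedure, so greater loss in the real arm is conjecture.

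Finally, an article may leave visit windows and follow-up after stopping to the full protocol. Silence on those would be no finding. Here, however, the article states both a timing rule and a withdrawal rule. The timing statements diverge outside full attendance, and the withdrawal rule leaves the consequence for outcome data open.

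**Conclusion.** The point holds as a defect in data collection. The post-treatment assessment is defined in two ways that part company for anyone who misses sessions or stops, withdrawal is not separated from the end of outcome collection, and nothing secures a PSQI from early stoppers. Taken literally, these rules leave such patients without a post-treatment value, so the efficacy comparison may be reduced to completers. That is a risk arising from the wording; no completer analysis is prescribed.

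The size and direction of any bias cannot be known from the document. On the assumption that early stoppers do not improve, 10% loss moves the completer comparison by between -0.18 and +0.45 points on a planned 2.7, with +0.27 when loss is equal in both arms. It is nil if loss is unrelated to outcome. The change should be made because it costs little and lost outcome data cannot be restored at the analysis stage.

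**What to change.** Reconcile Outcome measures, the Fig. 2 legend, Multimodal MRI data acquisition and Withdrawal criteria as follows:

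- Set the post-treatment PSQI, GSRS, SAS and SDS at 4 weeks from first treatment for all randomised patients, in both arms alike, whatever number of sessions was received.
- State that ending study treatment does not end outcome assessment unless the patient withdraws consent.
- State that arms are compared as randomised. A completer analysis may be added as a sensitivity analysis.

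The clinical grounds for ending treatment are left unchanged.

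The cost is the wording and a questionnaire contact for the few patients who stop early. The observed effect may also be smaller. With 10% of each arm stopping unimproved, the expected difference is 2.43, and power at 30 per arm is about 0.88, against about 0.94 for 2.7 (normal approximation, two-sided alpha 0.05, SD held at 3).

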#### Primary outcomes

The primary outcomes include MRI indicators and PSQI scale score. This study will focus on the following MRI indicators: the amplitude of low-frequency fluctuation (ALFF), seed-based functional connectivity (FC), cortical thickness, AD, FA, MD, RD, and Glu. ALFF and FC are the most common analysis indicators in fMRI, and their changes can reflect the functional activities of the brain [53]. Cortical thickness is a quantitative index of cortical morphology, which can directly reflect the changes of brain structure [54]. AD, FA, MD, and RD are all important indexes in DTI technology, which can be used to observe the integrity and connectivity of organizational structure [55]. Glu is an excitatory neurotransmitter involved in the occurrence and maintenance of sleep and wakefulness [56].

The PSQI comprises 19 self-evaluation items, among which 18 items generate 7 components. Each component is graded from 0 to 3, and the cumulative score of each component is the total score of PSQI, which ranges from 0 to 21. The PSQI is the most widely used sleep quality rating scale [57].

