**Methods:**

A total of 60 participants with CID and GI disorders will be randomly divided into two groups (real acupuncture group and sham acupuncture group; ratio of 1:1). Patients will receive 20 sessions (five sessions per week) of real acupuncture treatment or sham acupuncture treatment. The primary outcome is the aggregate score on the Pittsburgh Sleep Quality Index. Secondary outcomes are scores on the Gastrointestinal Symptom Rating Scale, Self-Rating Anxiety Scale, and Self-Rating Depression Scale. Multimodal MRI scans and clinical assessments will be performed both at baseline and post-treatment. Another 30 age-, sex-, and education-matched healthy subjects will be recruited as controls and will receive MRI scans and clinical evaluations.

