#### Imaging data analysis

The fMRI data will be preprocessed and analyzed using SPM12 (http://www.fil.ion.ucl.ac.uk/spm/) and CONN toolbox 18b (https://web.conn-toolbox.org/) with MATLAB 2014b (MathWorks, Inc., Natick, MA, USA). The sMRI data will be analyzed using the VBM toolbox within SPM12. DTI data will be processed using FSL Software on Linux. MRS data will be preprocessed using the commercially available software LCModel spectral-fitting package (version 6.3-1 N; Stephen Provencher, Inc., Oakville, ON, Canada). After standard preprocessing of each imaging modality, the following brain activity information will be calculated to examine the neural response to different treatments: the amplitude of low-frequency fluctuation, group independent component analyses, seed-based functional connectivity, cortical thickness, tract-based spatial statistics, and Glu. Finally, Pearson correlation analysis will be used to assess the association between changes in multimodal neuroimaging features and improvements in clinical outcomes in each group. MRI data from patients who received the drugs will be excluded because of the effects of the combination on brain function during the trial.

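### The abstract makes the PSQI total the only primary outcome, the Methods add eight MRI indicators as primary, and nothing says which of the nine decides the trial

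*Protocol article*

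**What the plan says.** The article gives two explicit outcome hierarchies.

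- **Abstract, Methods:** "The primary outcome is the aggregate score on the Pittsburgh Sleep Quality Index". It continues: "Secondary outcomes are scores on the Gastrointestinal Symptom Rating Scale, Self-Rating Anxiety Scale, and Self-Rating Depression Scale". MRI scans are mentioned as assessments but are ranked neither primary nor secondary.
- **Outcome measures, Primary outcomes:** "The primary outcomes include MRI indicators and PSQI scale score". The indicators are then listed as "the amplitude of low-frequency fluctuation (ALFF), seed-based functional connectivity (FC), cortical thickness, AD, FA, MD, RD, and Glu", which is eight and makes nine primary outcomes with PSQI.

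Three other places bear on the question.

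- **Sample size:** the calculation is for PSQI alone, on the premise that "the mean difference of PSQI scores between acupuncture and sham acupuncture was at least 2.7". "When α was 0.05, 1-β was 0.9, and standard deviation was 3, the calculated sample size was 27". The imaging side rests on a conventional range of 12 to 26 per group, with no effect size.
- **Clinical data analysis:** "A p value < 0.05 will be considered statistically significant". This is the only significance rule in the article. Imaging data analysis gives no threshold.
- **Background, study aims:** the first aim is to confirm efficacy against sham; the two aims that involve the brain are worded as exploration.

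**The concern.** Which result decides the trial has to be fixed before the data are seen. Here the abstract fixes it one way and the Methods another. Under the Methods version there is also no rule for combining nine results into one conclusion.

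Two things are at stake. First, a positive MRI indicator could be reported as a positive primary outcome when PSQI shows no difference, or the more convenient of the two hierarchies could be chosen afterwards. Second, the design figures of 5% error and 90% power were worked out for one PSQI comparison. They cease to describe the trial once eight further outcomes share primary rank.

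Condensing a full protocol into an article does not explain this, because both hierarchies are written out in the current text. A separate analysis plan could not resolve it without one of the two passages being changed.

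**Working it through.** **1. Reproduce the stated sample size.** Inputs from Sample size: difference 4.5 − 1.8 = 2.7, SD 3, alpha 0.05, power 0.90. Sidedness is not stated.

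- Standardised difference: 2.7 / 3 = 0.9.
- Normal approximation, two-sided: n per arm = 2 × (3 × (1.960 + 1.282) / 2.7)² = 25.94, so 26.
- Two-sample t-test (noncentral t), two-sided: power 0.889 at 26 per arm and 0.901 at 27.
- One-sided normal approximation: 22, which does not fit.

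The stated 27 is therefore the per-arm figure for a two-sided t-test of PSQI alone at 0.05. At the planned 30 per arm the same test has power 0.929.

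**2. Count the primary outcomes.** One in the abstract. In the Methods, PSQI plus ALFF, seed-based FC, cortical thickness, AD, FA, MD, RD and Glu: 1 + 8 = 9.

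**3. Case A: any one of the nine suffices, each as a single test at 0.05.** Both conditions are assumptions.

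- Independent tests: 1 − 0.95⁹ = 1 − 0.630 = 0.370.
- Equally correlated normal test statistics (correlation assumed):

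| Common correlation | Chance of at least one false positive |
|---|---|
| 0 | 0.37 |
| 0.3 | 0.33 |
| 0.4 | 0.30 |
| 0.5 | 0.27 |
| 0.7 | 0.20 |
| 0.9 | 0.12 |

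- Only the four diffusion indices correlated, at an assumed 0.8, and the rest independent: 0.31.

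The four diffusion indices come from the same DTI data, so independence is the upper case for nine single tests, not the likely one.

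**4. Case B: all nine must succeed.** A false claim then requires every test to pass, so the error is at most 5%. The chance of success cannot exceed the PSQI power alone (0.929 at 30 per arm) and would be lower by an amount that cannot be computed, because no effect sizes are given for the MRI indicators.

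**5. Case C, for illustration: any one suffices with Bonferroni protection.** The article does not propose this.

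- Alpha per outcome: 0.05 / 9 = 0.0056.
- PSQI power (t-test): 0.66 at 27 per arm, 0.72 at 30.
- For 90% PSQI power: 41 per arm by the normal approximation.

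**6. Case D: PSQI is the sole primary outcome.** Alpha stays 0.05, 27 per arm stands, and power is 0.93 at 30 per arm.

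Only Case D agrees with the abstract, the sample size calculation and the wording of the aims together.

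**The case against.** The strongest reply is that the article already implies a hierarchy. Efficacy is to be confirmed and mechanism explored, and only PSQI is formally powered. On that reading the Methods sentence is loose labelling and no one would claim efficacy from a change in ALFF. The implied hierarchy is real and shows which way to reconcile the text, but it does not cancel an explicit statement under the heading Primary outcomes.

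A reader might go further and infer that nine co-primary outcomes are tested at an unadjusted 0.05 and that the trial's family-wise error is about 37%. The documents do not support that.

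- The 0.05 rule closes the clinical analysis section. The imaging section states no threshold, adjusted or not. Correction within and across imaging measures may properly be left to an analysis plan that is not shown, so its absence is no finding.
- The 37% needs nine single tests, independence, and any one being enough. The article states none of these, and the shared source of the four diffusion indices argues against independence. If a measure were tested at many locations without correction, the error could exceed 37%, but the article does not say that this will happen.
- Co-primary is not the article's word. In its strict sense all outcomes must succeed, which does not inflate the error.

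The Bonferroni power loss likewise does not show that the stated sample size is wrong: for PSQI alone it is right.

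**Conclusion.** The point holds as a contradiction about the primary outcome together with a missing success rule. As written, the plan leaves room to choose the deciding result after the data are seen, and its stated alpha and power are true of the trial only if PSQI is the sole primary outcome.

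The size is conditional. If any one of nine single tests at 0.05 sufficed, the false-positive risk would be up to about 37% and would fall with positive correlation, though it would still be about 12% at a common correlation of 0.9. If all nine were required, the loss would be in power. The article does not settle which case applies, so no single error rate can be attributed to it.

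This must be fixed, because it concerns the trial's main conclusion and can be put right by rewording.

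**What to change.** Amend the Primary outcomes section so that the between-group difference in PSQI total at end of treatment is the sole primary outcome, tested at two-sided 0.05. This matches the abstract, the sample size calculation and the aims. State the sidedness in the Sample size section as well.

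Move all eight MRI indicators to secondary or exploratory mechanistic outcomes, and say that they cannot by themselves establish efficacy. Give them that rank in the abstract too, where they now have none.

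If the investigators want MRI indicators to remain primary, the alternative is to state which combination of results counts as success, name a multiplicity procedure, and redo the sample size on that basis.

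The recommended route needs no extra patients: 27 per arm still stands and power at 30 per arm is about 0.93. Its cost is that imaging results can no longer be called primary.
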